## Abstract

**Background:**

Oxytocin is effective in reducing labor duration, but can be associated with fetal and maternal complications such as neonatal acidosis and post-partum hemorrhage. When comparing discontinuing oxytocin in the active phase with continuing oxytocin infusion, previous studies were underpowered to show a reduction in neonatal morbidity. Thus, we aim at evaluating the impact of discontinuing oxytocin during the active phase of the first stage of labor on the neonatal morbidity rate.

**Methods:**

STOPOXY is a multicenter, randomized, open-label, controlled trial conducted in 20 maternity units in France. The first participant was recruited January 17th 2020. The trial includes women with a live term (≥37 weeks) singleton, in cephalic presentation, receiving oxytocin before 4 cm, after an induced or spontaneous labor. Women aged < 18 years, with a lack of social security coverage, a scarred uterus, a multiple pregnancy, a fetal congenital malformation, a growth retardation <3rd percentile or an abnormal fetal heart rate at randomization are excluded. Women are randomized before 6 cm when oxytocin is either continued or discontinued. Randomization is stratified by center and parity. The primary outcome, neonatal morbidity is assessed using a composite variable defined by an umbilical arterial pH at birth < 7.10 and/or a base excess > 10 mmol/L and/or umbilical arterial lactates> 7 mmol/L and/or a 5 min Apgar score < 7 and/or admission in neonatal intensive care unit. The primary outcome will be compared between the two groups using a chi-square test with a *p*-value of 0.05. Secondary outcomes include neonatal complications, duration of active phase, mode of delivery, fetal and maternal complications during labor and delivery, including cesarean delivery rate and postpartum hemorrhage, and birth experience. We aim at including 2475 women based on a reduction in neonatal morbidity from 8% in the control group to 5% in the experimental group, with a power of 80% and an alpha risk of 5%.

**Discussion:**

Discontinuing oxytocin during the active phase of labor could improve both child health, by reducing moderate to severe neonatal morbidity, and maternal health by reducing cesarean delivery and postpartum hemorrhage rates.

**Trial registration:**

Clinical trials NCT03991091, registered June 19th, 2019.

## Background

### Rationale

More than one in two women delivering in France is administered oxytocin during labor, either as part of induction of labor or because of poor uterine contractions [1]. Oxytocin is indeed effective in increasing frequency and intensity of uterine contractions and therefore in reducing labor duration [2, 3].

The most important side effect of oxytocin infusion is uterine hyper-stimulation, which has been shown to occur in more than 30% of women induced with oxytocin [4, 5]. By causing uterine hyper-stimulation, oxytocin may lead to or aggravate an abnormal fetal heart rate, contributing to neonatal acidosis. Acidosis accounts for a significant proportion of term neonatal morbidity due to related complications such as hospitalization in neonatal intensive care units, but also neonatal death or cerebral palsy in the most severe cases. In addition, the effectiveness of oxytocin in decreasing the cesarean delivery rate has not been demonstrated [6, 7]. And, its administration is potentially associated with maternal complications, such as post-partum hemorrhage [8].

Obstetric situations requiring oxytocin administration before 4 cm of dilation are induction of labor, with or without previous cervical ripening and labor dystocia, i.e. non-progression of the cervical dilation during the latent phase [9–11]. One assumption is that, once women requiring oxytocin during the latent phase enter the active phase, natural oxytocin takes over from synthetic oxytocin [12]. Thus, in the active phase, oxytocin could be discontinued, reducing exposure duration and therefore reducing the risk of complications, in particular neonatal complications such as hypoxia, without compromising the chances of vaginal delivery. It can therefore be hypothesized that discontinuation of oxytocin in the active phase of labor (from 6 cm) in women who received oxytocin in the latent phase or for an induction of labor could reduce neonatal morbidity.

### Previous published studies

Previous studies have evaluated the effect of discontinuation of oxytocin when reaching the active phase of labor on duration of the active phase of labor [13–17]. All these studies but one [15] were randomized, none used blinding, and the largest sample size was of 342 women (168 vs 174) [16]. Most of these studies, as well as the metanalysis [12] including them, showed a longer length of active phase of labor in the discontinuation of oxytocin group (in the metanalysis the mean difference was 27.65 min, 95%CI 3.94–51.36). None of these previous published trials, nor the meta-analysis combining these trials [12] showed an increase in the cesarean delivery rate in the discontinuous oxytocin group, on the contrary, the meta-analysis showed a significant decrease in the cesarean delivery rate in the discontinuous oxytocin group (9.3% compared with 14.7%; RR 0.64, 95%CI 0.48–0.87). This supports the assumption that natural oxytocin takes over from synthetic oxytocin in the active phase of labor and allows achieving vaginal delivery.

Only three studies reported the rates of postpartum hemorrhage (PPH) [14, 15, 18], one showed no differences in its rate (6.4% vs 6.3% [18]) and the other two showed a decrease in the PPH rates in the discontinuous oxytocin group without reaching statistical significance, probably due to a lack of power (16% vs 22% [14] and 1.4% vs 3% [15]). The dose and duration of oxytocin infusion is known to be associated with PPH [8], reducing these could therefore reduce the PPH risk.

Concerning neonatal morbidity, only two trials [14, 16] evaluated the impact of discontinuation of oxytocin on the rate of neonatal acidosis. One showed a two-fold reduction of neonatal acidosis in the discontinuation group (6% versus 3% umbilical arterial pH < 7.10), but the small number (*n* = 100/group) did not lead to a statistically significant difference. The other study showed no significant difference between the two groups (4% vs 5% for pH < 7.10 and 9.8% vs 7.1% for Neonatal Intensive Care Unit (NICU) admission).

## Methods

STOPOXY is a multicenter, randomized, open-label, controlled trial conducted in France.

### Setting

In 20 maternity units, in 15 cities in France.

### Population

The STOPOXY trial includes:
Women receiving oxytocin during the latent phase of the 1st stage of labor, before 4 cm of cervical dilation, including women with an induction of labor using cervical ripening or oxytocinWith a term pregnancy (≥37 weeks)Singleton pregnancyFetus in cephalic presentationSpeaking and reading French languageAffiliated to social securityWho have signed the consent form

Exclusion criteria are as follows:
Women with a scarred uterusFetus with a congenital abnormalityFetal growth retardation <3rd percentile for gestational ageAbnormal fetal heart rate at randomizationMaternal age < 18 yearsWomen participating in another trial involving medication

### Objectives and endpoints

Our main objective is to measure the impact of a discontinuous administration of oxytocin during the active phase of the first stage of labor on the neonatal morbidity rate. Neonatal morbidity is assessed using a composite variable defined by: an umbilical arterial pH at birth < 7.10 and/or a base excess > 10 mmol/L and/or umbilical arterial lactates> 7 mmol/L and/or a 5 min Apgar score < 7 and/or admission in neonatal intensive care unit (NICU).

Our secondary objectives are to measure the impact of a discontinuous administration of oxytocin during the active phase of the first stage of labor on:

Neonatal acidosis and its severity:
Umbilical arterial cord pH at birth less than 7.20Umbilical arterial cord pH at birth less than 7.10Umbilical arterial cord pH at birth less than 7.00Need for hypothermia

Other neonatal complications:
Need for resuscitation at birthTransfer to a neonatal care unitLength of hospital stay

Mode of delivery:
Cesarean delivery rateRate of cesarean delivery for abnormal fetal heart rateInstrumental vaginal delivery rateRate of instrumental delivery for abnormal fetal heart rate

Fetal and maternal complications during labor and delivery:
Labor duration (active 1st stage, 2nd stage)Uterine hyper-stimulation, defined by periods with more than five uterine contractions in 10 min during laborNeed for fetal scalp blood testing during laborRate of fetal occipito-posterior positionMaternal fever during labor, defined by a maternal temperature > 38 °CPost-partum hemorrhage, defined by an estimated blood loss > 500 mL

Birth experience:
Post-partum women’s satisfaction using the labor agentry scale (LAS)A 2 months postpartum survey assessing women’s birth experience, women’s well-being using Edinburgh Postnatal Depression Scale (EPDS) and mother-child relationship, especially breastfeeding.

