### Power calculation

A prospective population-based cohort study was conducted in France in 2015 assessing French practices of induction of labor, MEDIP (MEthodes de Déclenchement et Issues Périnatales) [19]. In this study, data on oxytocin use and neonatal outcomes is available. In the French MEDIP cohort, among women receiving oxytocin under standard care (as in our control group), 8% of neonates had at least one criterion of the primary endpoint of STOPOXY trial.

We hypothesize a decrease from 8% with standard care (i.e. control group) to 5% with discontinuation of oxytocin (i.e. experimental group). Assuming this decrease, we need a sample size of 1125 women in each group, for a power of 80% and an alpha risk of 5% with the use of a bilateral test. Because some women could be included and randomized, but never reach 6 cm of cervical dilation, and thus not receive the intervention, we plan to include 10% more women. We suppose that this number will correspond to the number of women having a cesarean delivery before starting the intervention, i.e. before 6 cm. Therefore, to reach statistical significance, we would like to include 2475 women in our trial.

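### The base-excess criterion of the primary composite points the wrong way: read literally it describes alkalosis, although the composite targets acidosis

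*Protocol article*

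**What the plan says.** The Objectives and endpoints section of the protocol article defines neonatal morbidity as any one of five criteria: arterial cord pH below 7.10, the base-excess criterion, arterial lactates above 7 mmol/L, a 5-minute Apgar score below 7, or NICU admission. The base-excess and lactate criteria read "and/or a base excess > 10 mmol/L and/or umbilical arterial lactates> 7 mmol/L". The Methods paragraph of the Abstract has the same direction: "an umbilical arterial pH at birth < 7.10 and/or a base excess > 10 mmol/L".

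The Rationale states the harm that the trial addresses: "oxytocin may lead to or aggravate an abnormal fetal heart rate, contributing to neonatal acidosis".

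The Power calculation section ties the planning rate to this composite. In the MEDIP cohort, under standard care, "8% of neonates had at least one criterion of the primary endpoint of STOPOXY trial". The sample size is "1125 women in each group, for a power of 80% and an alpha risk of 5% with the use of a bilateral test", with 10% added to give 2475.

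**The concern.** Base excess falls below zero as metabolic acidosis develops. A value above +10 mmol/L means marked alkalosis. The acidosis criterion can be written as a base deficit above 10 or as a base excess below -10; the article combines the name of one form with the inequality of the other.

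The definition feeds the one comparison on which the trial is judged, the chi-square test in the section Analysis of the primary endpoint. If the derivation were programmed from this text on signed values, two things would follow:

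- A neonate whose only qualifying feature is a strongly negative base excess, say -12 mmol/L, would be classed as free of morbidity.
- A neonate with a base excess above +10 mmol/L would be classed as having morbidity.

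The analysed endpoint could then also differ from the one behind the 8% planning rate, since the article does not say in which direction MEDIP was counted.

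**Working it through.** **Direction of the three acid-base criteria, as printed**

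| Criterion | Printed inequality | What it selects |
|---|---|---|
| Arterial pH | < 7.10 | acidosis |
| Base excess | > 10 mmol/L | alkalosis |
| Arterial lactates | > 7 mmol/L | acidosis |

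**Does the article settle the direction elsewhere?** No. The Abstract and the Objectives and endpoints section agree with each other. Neither uses the term base deficit or states a sign convention. The secondary acidosis outcomes use pH cut-offs and need for hypothermia only.

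**Could a minus sign have been lost when the PDF was read?** That would not explain it. A base excess > -10 would count neonates with normal values. The inequality itself has to be reversed.

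**Reproducing the planned sample size.** Inputs from the Power calculation section: p1 = 0.08, p2 = 0.05, two-sided alpha 5% (z = 1.960), power 80% (z = 0.842), difference d = 0.03, mean rate 0.065.

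- Without continuity correction: n = [1.960 × √(2 × 0.065 × 0.935) + 0.842 × √(0.08 × 0.92 + 0.05 × 0.95)]² / 0.03² = 1059 per arm after rounding up.
- With continuity correction: n' = (n/4) × [1 + √(1 + 4/(n × d))]² = 1125 per arm, an exact match.
- Total: 2 × 1125 × 1.10 = 2475, an exact match.

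**What losing the component could cost.** The article gives no share of events that qualify by base excess alone, so this share, f, is an assumption. Take p1 = 0.08 × (1 - f) and p2 = 0.05 × (1 - f), which keeps the relative risk at 0.05/0.08 = 0.625. With n = 1125 per arm and the chi-square test without continuity correction,

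power = Φ{[√n × (p1 - p2) - 1.960 × √(2p̄(1 - p̄))] / √(p1(1 - p1) + p2(1 - p2))}, where p̄ is the mean of p1 and p2.

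| f (assumed) | Control rate | Experimental rate | Power |
|---|---|---|---|
| 0% | 8.0% | 5.0% | 82.3% |
| 5% | 7.6% | 4.75% | 80.2% |
| 10% | 7.2% | 4.5% | 77.9% |
| 20% | 6.4% | 4.0% | 72.7% |
| 30% | 5.6% | 3.5% | 66.7% |

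The first row exceeds the planned 80% because 1125 includes the continuity correction and this power formula does not. The table leaves out alkalotic neonates wrongly counted as events, because the article gives nothing from which to estimate their number.

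**The case against.** The strongest reply is that this is a slip of notation that would mislead no one in the field. The criterion stands between a low-pH and a high-lactate criterion, in a trial whose rationale is acidosis, so the only coherent reading is a base deficit above 10 mmol/L. The source is also a journal article; the e-CRF field, its sign convention and the derivation belong to documents not shown and may be correct there. Both parts are fair. They mean that the article is no evidence of miscoded data. They do not make the printed definition right: it is wrong in both places, and a primary endpoint should be programmable from its own text.

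Three stronger readings are tempting and are not supported:

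- *The trial fails to capture acidosis.* Literal coding would empty one component only. Acidotic neonates who also meet the pH, lactate, Apgar or NICU criterion would still be counted.
- *Units record the value with different signs, so the same neonate is classified differently by site.* No section says or suggests this. The article describes a common electronic case report form and data collection by study technicians, which neither shows nor excludes mixed conventions.
- *The power calculation is undermined.* This needs the 8% to have been counted in the acidosis direction and the trial to be coded in the opposite one. The article shows neither. The share f is also unanchored: the acid-base criteria overlap, so it may be small, and at 5% power is still 80.2%.

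**Conclusion.** The point holds as an error in the definition of the primary endpoint. As printed, the base-excess criterion has the wrong direction in the Abstract and in Objectives and endpoints, and nothing in the article corrects it. Confidence in this is high, because it rests on the printed inequality and on the ordinary meaning of base excess.

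The consequence is limited to neonates who qualify by base excess alone, plus any alkalotic values wrongly counted, and it arises only if the text is applied literally to signed values. The size is unknown. The range from 82.3% down to 66.7% power is an illustration that assumes 1125 analysed per arm, an unchanged relative effect and an assumed share of 0% to 30%; it is not an estimate of loss in this trial. The figures of 1125 per arm and 2475 in total stand if the 8% was counted in the acidosis direction.

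**What to change.** 1. Replace the criterion with base excess < -10 mmol/L (base deficit > 10 mmol/L) wherever the endpoint is defined: the Abstract, Objectives and endpoints, and the corresponding text of the full protocol and SAP.
2. Check that the e-CRF sign convention and the endpoint derivation use that direction. If values have already been entered, query any positive base excess of 10 or more.
3. Confirm that the 8% MEDIP rate was counted in the same direction, and say so in the Power calculation section. If it was not, the planning rate needs to be recounted.
4. Recruitment has begun and the trial is open-label, so date and document the correction before outcomes are compared by arm.

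The cost is a one-line text correction, a check of the form and the derivation, and one query to the holders of the MEDIP data. It adds no participants and no procedures.

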### Informed consent and inclusion

The initial information on the trial can be delivered before labor, during the women’s last prenatal visits by the midwife or obstetrician, during the visit at the outpatient clinic or during the birth preparation classes. The information is also distributed using posters, in the waiting rooms, emergency rooms and in the outpatient’s clinic.

Women can also be screened and informed during induction of labor or during onset of labor in case of spontaneous labor, in the labor ward. In all cases, because the cervical modifications during induction of labor are slow, especially in case of cervical ripening and during the latent phase, the delay between the final information and the inclusion appears long enough for the women to decide on their participation. All information on the chronology of the study is available in Table 1.

**Table 1 Tab1:** Timeline table summarizing the chronology of the study

Time-point	Study period					
	Enrollment	Enrollment and allocation	Post-allocation			Post allocation and close-out
	D-30 (end of pregnancy)	D0 (before 6 cm)	D0 (during labor)	D0 (immediate postpartum)	D0 (after delivery in labor ward)	M2 postpartum
**Enrollment**						
Information	X					
Signature of the consent form		X				
Inclusion		X				
Randomization		X				
**Intervention**			X			
**Assessment**						
Adverse events			X	X	X	
Primary endpoints				X	X	
Secondary endpoints				X	X	X
Labor Agentry Scale Questionnaire					X	
Experience of childbirth questionnaire, EPDS						X
Breastfeeding assessment						X

Maternal pain during the onset of labor could be a concern in obtaining an informed consent. But, it has to be noted that the information on the study is mostly given before labor. Also, in the 20 participating maternity units the rate of epidural during labor is high (at least 80%). Epidural is not an inclusion criterion in the STOPOXY trial, however, most of the included women will probably receive an epidural.

The obstetrician and the midwives responsible for the labor and delivery ward are in charge of screening the includable women in the study. The inclusion is then be performed by the investigator, who will complete a computerized inclusion form, accessible 24 h on line and developed by the Cleanweb® company. The inclusion and exclusion criteria have to be met in order to include the women.

All the maternity units volunteering to participate in the STOPOXY trial are part of the Groupe de Recherche en Obstétrique et Gynécologie (GROG) network. The GROG network is a national research network affiliated with the CNGOF (Collège National des Gynécologues Obstétriciens Français).

### Oxytocin infusion protocol and randomization

During the latent phase, oxytocin is administered according to national guidelines, i.e. low dose oxytocin infusion of less than 4 mUI/min with increments every 30 min, without exceeding a 20 mUI/min flow rate [9].

Women are included and randomized in two groups before 6 cm, during the latent phase (Supplementary Material 1):
The experimental group corresponds to discontinuation of oxytocin at the beginning of the active phase of the 1st stage of labor, i.e. oxytocin infusion is stopped beyond a cervical dilation equal or greater than 6 cm. In the experimental group, oxytocin can be re-started, if necessary, after 2 h of labor arrest (no progression of the cervical dilation and no progression of the fetal head).The control group corresponds to the standard care in France, i.e. when oxytocin is started during the latent phase of the 1st stage administration of oxytocin is continued during the active 1st stage and during the 2nd stage if the fetal heart rate is reassuring. As in French standard practice, the oxytocin infusion is maintained with no increments if cervical dilation progresses. If needed (abnormal fetal heart rate, uterine hyperstimulation) the infusion can be stopped.

The randomization is computerized and accessible 24 h on line. Subjects are distributed between the two groups at a ratio of 1:1. The randomization is stratified on the center and parity (nullipara/multipara). The stratification by center will allow considering the possible variations of practices between centers during labor or delivery (e.g. modalities of epidural analgesia, type of analgesic products used, etc.). Specific information on the practices is also collected in the electronic case report form (e-CRF). The stratification by parity is needed because multiparous and nulliparous women differ on several secondary endpoints such as duration of labor and mode of delivery.

Among women included in the STOPOXY trial, some will have a spontaneous labor and others an induction of labor including induction by oxytocin only or cervical ripening. Induction protocols and particularly cervical ripening methods (Prostaglandins E1, Prostaglandins E2, and mechanical methods) could differ between centers but this potential difference will be taken into account by the stratification by center.

Each change in dose of oxytocin (increments) after 6 cm of cervical dilation and until delivery will be prospectively collected and reported by the midwife or obstetrician on a specific form. The time, type of modification of infusion, reason for the change, cervical dilation and oxytocin flow will be specified.

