### Choice of open-label design

The open-label design was chosen for several reasons, the main being that in case of a blinded trial, the need for un-blinding would have been too frequent. Indeed, some of the previous studies showed that during the active phase of labor, 30 to 40% of the women with a discontinued administration of oxytocin required a re-start of oxytocin after a two-hour arrest of labor [14, 15]. Another situation requiring to un-blind the randomization group is in case of non-reassuring fetal heart rate which was the case in up to 8% of the women in Saccones’ metanalysis [12]. Indeed, in the context of non-reassuring fetal heart rate (FHR) it is important for the obstetrician to know the treatment group in order to stop the oxytocin infusion to reduce uterine contractility.

The choice of this design was discussed several times on the GROG’s meetings and the final decision was to choose an open-label design. The advantages are those described above, and the bias related to the open label design will be low considering that the primary endpoint is a composite variable of objective criterions.

Apart from oxytocin administration the labor management does not differ between the two groups. The condition to re-start oxytocin in the experimental group is well described, i.e. 2 h of labor arrest (no progression of the cervical dilation and no progression of the fetal head).

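### Allocation is issued before the arms differ at 6 cm in an open-label trial, which opens an avoidable window for bias and leaves 2475 women with about 75–78% power under intention-to-treat, not 80%

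*Protocol article*

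**What the plan says.** The section on oxytocin infusion and randomization states: "Women are included and randomized in two groups before 6 cm, during the latent phase". In the same section, latent-phase oxytocin follows one national guideline for everyone. The experimental arm departs from the control arm only once dilation is 6 cm or more. Table 1 likewise places randomization before 6 cm and the intervention afterwards. On logistics: "The randomization is computerized and accessible 24 h on line".

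The trial is open-label. The section defending that choice states: "Apart from oxytocin administration the labor management does not differ between the two groups".

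The power calculation foresees that "some women could be included and randomized, but never reach 6 cm of cervical dilation, and thus not receive the intervention". It supposes these are women with a cesarean before 6 cm and adds 10% for them, going from 1125 per group to 2475 in total. The primary endpoint section then places every included and randomized woman in the intention-to-treat analysis.

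The exclusion for "abnormal fetal heart rate at randomization" applies at allocation, not at the point where the arms diverge.

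**The concern.** Two consequences follow from issuing the allocation early.

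First, between allocation and 6 cm, staff who know whether oxytocin will be stopped or continued are still titrating it, examining the woman and deciding on cesarean. The reasons given for open label are restarts after labor arrest in the active phase and the need to know the arm when the fetal heart rate is non-reassuring. They explain why staff must know the arm once the arms differ, not why they must know it sooner. The argument that the endpoint is objective concerns outcome assessment, not care given before 6 cm. The form for dose changes starts only after 6 cm.

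Second, women who deliver before 6 cm receive the same planned care in both arms, yet they count in the primary comparison. They carry no treatment contrast and pull the two arms together. Adding 10% replaces their number but does not undo that dilution.

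**Working it through.** **Inputs (Power calculation section unless noted).** Control 8%, experimental 5%; 1125 per group; 80% power; 5% alpha, "with the use of a bilateral test"; 10% addition; 2475 in total. Ratio 1:1 (randomization section). All randomized women analysed (primary endpoint section). Morbidity in women who never reach 6 cm is not given. I assume 8% in both arms and show 5% to 15%.

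**1. Reproduce the stated size.** With p̄ = (p1 + p2)/2 and d = p1 − p2,

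n = [1.96·√(2p̄(1−p̄)) + 0.8416·√(p1(1−p1) + p2(1−p2))]² / d².

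For 8% versus 5%, n = 1059 per group. The continuity-corrected size is (n/4)·[1 + √(1 + 4/(n·d))]² = 1125, which matches exactly. Then 2 × 1125 = 2250, and 2250 × 1.10 = 2475.

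**2. Share with no contrast.** 2475 − 2250 = 225, and 225/2475 = 9.1%.

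**3. Diluted rates under intention-to-treat.** Control: 0.909 × 8% + 0.091 × 8% = 8.0%. Experimental: 0.909 × 5% + 0.091 × 8% = 5.27%. Difference: 0.909 × 3 = 2.73 points.

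**4. Power at 2475 (1237.5 per group).** Power = Φ[(d − c − 1.96·SE0)/SE1], where SE0 = √(2p̄(1−p̄)/n), SE1 = √((p1(1−p1) + p2(1−p2))/n), and c = 1/n with continuity correction or 0 without. For step 3, SE0 = 0.01001 and SE1 = 0.00999.

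- Uncorrected: (0.02727 − 1.96 × 0.01001)/0.00999 = 0.767, power 77.8%.
- Corrected: (0.02646 − 1.96 × 0.01001)/0.00999 = 0.686, power 75.4%.

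| Assumed morbidity if 6 cm is never reached | Rates compared | Corrected | Uncorrected |
|---|---|---|---|
| 5% | 7.73% vs 5.00% | 77.0% | 79.4% |
| 8% | 8.00% vs 5.27% | 75.4% | 77.8% |
| 15% | 8.64% vs 5.91% | 71.8% | 74.3% |

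**5. What would restore 80%.** With allocation at 6 cm, 1125 per group at 8% versus 5% gives 80.0% corrected and 82.3% uncorrected. With allocation left as it is, the rates in step 3 require about 2758 women (corrected) or 2614 (uncorrected).

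**6. The behavioural risk.** No figure in the article allows its size to be computed.

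**The case against.** The strongest reply is that randomizing before the point of divergence and analysing by intention-to-treat is a legitimate, disclosed choice. Safeguards exist: both arms follow the same latent-phase guideline, and the compliance section has the allocated treatment, total dose and duration monitored throughout, not only after 6 cm. The interval between allocation and 6 cm is not stated and may be short. The article is condensed and refers to supplementary material that is not shown. All of this stands, and it limits the first consequence to a risk.

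The power loss could also be repaired by a larger sample without moving the randomization point. That is true, but it leaves the window open.

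The 8% comes from a cohort of women receiving oxytocin under standard care, with no stated restriction to those reaching 6 cm, who may be at lower risk. Suppose control morbidity among them were 7% with the same relative reduction (7% × 5/8 = 4.375%; an assumption). Then 1125 per group would give 77% uncorrected and 74% corrected. So the 80% after the fix is conditional. The present design would fall as well: with 8% in women not reaching 6 cm, the rates become 0.909 × 7% + 0.091 × 8% = 7.09% and 0.909 × 4.375% + 0.091 × 8% = 4.70%, and 2475 women give about 71% and 68%.

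A reader might infer that moving the allocation saves patients, or that 2475 women randomized at 6 cm (86% uncorrected, 84% corrected) is the fair comparison. Neither follows. Randomizing 2475 at 6 cm needs about 2475/0.909 = 2722 consented women, and randomizing 2250 still needs about 2475. A gain in power for cesarean cannot be claimed either: the article does not say when the trials behind its meta-analysis rates randomized, so those rates may already include early cesareans.

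**Conclusion.** The point holds in two parts of different strength. The window between allocation and 6 cm is real and avoidable, but its effect is unknown. A reader might infer that care before 6 cm did differ by arm; nothing in the article shows that.

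The power shortfall follows from the article's own figures plus one assumption. The 10% addition would preserve 80% only if women not reaching 6 cm were left out, and the stated analysis keeps them in. With 9.1% such women and 8% morbidity among them, 2475 gives about 75% (corrected) to 78% (uncorrected), and 72–79% for morbidity of 5% to 15%. A reader might also infer that these women drop out of the comparison. They do not: they are analysed, and the harm is dilution. Leaving them out afterwards would not be a clean remedy, because reaching 6 cm could itself depend on care given with the arm known.

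The dilution figure assumes that care before 6 cm is the same in both arms. If it were not, these women would carry that difference into the result instead.

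**What to change.** Keep information, consent, eligibility screening and the inclusion form before 6 cm. Have the existing online system issue the allocation when a dilation of 6 cm or more is recorded, and check the existing heart-rate exclusion at that moment. State the target as 2250 women so randomized, with the condition that 8% versus 5% applies to women who reach 6 cm.

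Recruitment began in January 2020, so a transition rule is needed. Women already randomized earlier remain in the intention-to-treat analysis in their allocated arm. For them, report by arm the proportion reaching 6 cm and the number of cesareans before 6 cm, as a check on care in the window. Because they still dilute the effect, the power of the mixed sample should be recalculated from their actual number.

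The cost is an amendment, a changed trigger in the online system, a log-in during labor, and the loss of some rapid labors that pass 6 cm before allocation. About 2475 women must still consent.

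If the randomization point is not moved, restate the power of 2475 under intention-to-treat as about 75–78%, with its assumption.
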